## Secondary Objectives

To prospectively evaluate:

- the efficacy of 2 week loading or 4 week priming followed by concentration targeted dosing of ribavirin in combination with peginterferon alpha-2a in interferon naïve patients with chronic hepatitis C (CHC) virus genotype 1 infection as compared to standard-of-care dosing of ribavirin in combination with peginterferon alpha-2a as evaluated by the proportion of patients achieving VRVR ( “very rapid virologic response” i.e. HCV-RNA below 1000 U/mL at treatment day 7 after intiation of PEG-interferon), RVR (“rapid virologic response”, undetectable HCV-RNA at treatment day 28 after intiation of PEG-interferon), cEVR (“complete early virologic response”, i.e. undetectable HCV-RNA at treatment week 12 after intiation of PEG-interferon), and pEVR (“partial early virologic response”, i.e. decline of HCV-RNA by at least 2 log10 compared with baseline at treatment week 12 after intiation of PEG-interferon).
- the efficacy of 2 week loading or 4 week priming followed by concentration targeted dosing of ribavirin in combination with peginterferon alpha-2a in interferon naïve patients with chronic hepatitis C (CHC) virus genotype 1 infection is superior to standard-of-care dosing of ribavirin, peginterferon alpha-2a therapy as evaluated by sustained virological response (SVR, undetectable HCV-RNA 24 weeks after end of treatment).
- the predictive value of monitoring of viral load at day 0 (before the 1st dose of peginterferon alpha-2a), day 3, day 7 (before the 2nd dose of peginterferon alpha-2a), and day 28 (before the 5th dose of peginterferon alpha-2a) for determining which patients will obtain a sustained virological response (SVR) when treated with ribavirin and peginterferon alpha-2a therapy.
- the association between the trough concentrations of ribavirin (day 1, day 3, day 7, day 28, week 8, week 12, week 16, and end-of-treatment), and the therapeutic efficacy of ribavirin and peginterferon alpha-2a therapy.
- The association between plasma IP-10 (days 0, 1, 3, 7, and 14, and weeks 8, 18, and 24), and the therapeutic efficacy of ribavirin and peginterferon alpha-2a therapy.
- the effect of IL-28B polymorfism on the viral kinetic response and SVR.
- the effect of baseline vitamin D concentrations on the viral kinetic response and SVR.
- the association between liver histology as evaluated by the Ishak scoring system (modified HAI score) and steatosis grading, and the therapeutic efficacy of peginterferon alfa-2 combination therapy with ribavirin.
- the association between liver stiffness as evaluated by the FibroScan and the therapeutic efficacy of peginterferon alfa-2 combination therapy with ribavirin.
- the association between liver fibrosis as evaluated by the GUCI and APRI indexes as well as hyaluronic acid, and the therapeutic efficacy of peginterferon alfa-2 combination therapy with ribavirin.
- the association between body mass index (BMI), waist circumference, weight and age, and the therapeutic efficacy of peginterferon alfa-2 combination therapy with ribavirin.
- the predictive value of monitoring CD56 negative NK, CD4+ CD38+, CD8+ CD38+, CD8+CD16+, Foxp3+, and pDC (CD303+) cells in peripheral blood and liver biopsies as analyzed by FACS prior to and after the initiation of therapy for determining which patients will obtain a sustained virological response (SVR) when treated with peginterferon alfa-2 and ribavirin combination therapy.
- the predictive value of quantifying mRNA expression in pre-treatment liver biopsies for IFI-27, IP-10, CXXL-6, IL-2, IL-8, IL-10, -IFN, TNF-, KRT19, COL1A1, MMP7, TIMP1, FASL, AIF1 for determining which patients will obtain a sustained virological response (SVR) when treated with peginterferon alfa-2 and ribavirin combination therapy.

Others:

To prospectively evaluate:

- the predictive value of monitoring the trough concentrations of ribavirin (day 1, day 3, day 7), and the final steady-state concentration of ribavirin.
- the safety of peginterferon alpha-2a combination therapy with concentration targeted dosing of ribavirin in combination peginterferon alpha-2a, based on accumulated number of adverse events and severe adverse events as well as the impact on quality of life during treatment and follow-up phase.
- the safety of peginterferon alpha-2a combination therapy with concentration targeted dosing of ribavirin in combination peginterferon alpha-2a, with particular regards to the number of patients in each treatment arm developing anemia grade 1 (10.5-9.5 g/dL), grade 2 (9.4-8.0 g/dL), grade 3 (7.9-6.5 g/dL), and grade 4 (<6.5 g/dL).

# STUDY design

## Overview of Study Design and Dosing Regimen

This study will be conducted as a phase III, open label, multicenter trial. A total of 105 patients will be randomized to one of three possible treatment groups.

**Group A:** (“Loading”): PEG-IFN α-2a 180 g/week plus loading (≥26 mg/kg/day for 2 weeks followed by ≥13 mg/kg/day) and concentration targeted (≥ 2.5 mg/L (10.25 μmol/L) 28 days after initiation of ribavirin therapy) dosing of ribavirin and response guided treatment duration (RVR 24 weeks, non-RVR 48 weeks, pEVR consider 72 weeks), follow-up period 24 weeks.

**Group B**: (“Priming”): Standard-of-care dosing of ribavirin (≥13 mg/kg/day) without PEG-IFN for 4 weeks followed by 24-48 additional weeks of PEG-IFN α-2a 180 g/week plus standard-of-care dosing of ribavirin (≥13 mg/kg/day) and concentration targeted (≥ 2.5 mg/L (10.25 μmol/L) 28 days after initiation of ribavirin therapy) dosing of ribavirin and response guided treatment duration (RVR 28 weeks, non-RVR 52 weeks, pEVR consider 76 weeks), follow-up period 24 weeks.

**Group C:** (“Standard-of-Care”): PEG-IFN α-2a 180 g/week plus standard-of-care dosing of ribavirin (≥13 mg/kg/day without any measurement of ribavirin concentration) and response guided treatment duration (RVR 24 weeks, non-RVR 48 weeks, pEVR consider 72 weeks), follow-up period 24 weeks.

## Number of Patients

A total of 105 patients will be enrolled in the study: 35 patients in group A, 35 patients in group B and 35 patients in group C.

## Centers

This study will be conducted at experienced centers in Sweden, Norway, Denmark, and Finland willing to include at least 5 patients. Only those centers qualified by training and experience in the clinical and research management of patients with CHC will be invited to participate.

# STUDY POPULATION

## Target Population

Men and women ≥ 18 years old with CHC genotype 1 will be enrolled in this study. Patients must have HCV-RNA ≥ 15 IU/mL, and compensated liver disease (Child-Pugh Grade A). Patients with other forms of liver disease, human immunodeficiency virus (HIV) infection, hepatocellular carcinoma, anemia, pre-existing severe depression or other psychiatric disease, significant cardiac disease, renal disease, seizure disorders, or severe retinopathy will not be included.

## Inclusion Criteria

To be eligible for this trial, patients must have the following documented:

Inclusion Criteria:

- Written informed consent
- Male and female patients 18 years of age
- Serologic evidence of chronic hepatitis C infection by an anti-HCV antibody test
- Serum HCV-RNA 15 IU/mL.
- HCV genotype 1 infection confirmed within the past 2 years preceding the initiation of test drug dosing.
- Compensated liver disease (Child-Pugh Grade A clinical classification)
- Patients with cirrhosis or transition to cirrhosis must have an abdominal ultrasound, CT scan, or MRI scan without evidence of hepatocellular carcinoma and a serum AFP ≤100 ng/mL within 2 months of randomization
- Negative urine or blood pregnancy test (for women of childbearing potential) documented within the 24-hour period prior to the first dose of study drug
- All fertile males and females receiving ribavirin must be using effective contraception during treatment and during 4 months for female patients / 7 months for male patients after end of treatment
- Subject must weigh between 45 and 105 kg at screening

## Exclusion Criteria

Patients with any of the following will not be eligible for participation:

Exclusion Criteria:

- Women with ongoing pregnancy or breast feeding
- IFN/ peg-interferon with or without ribavirin therapy at any previous time
- Therapy with any systemic anti-viral, anti-neoplastic or immunomodulatory treatment (including supraphysiologic doses of steroids and radiation) £6 months prior to the first dose of study drug
- Any investigational drug 6 weeks prior to the first dose of study drug.
- HCV genotype 2, 3, 4, 5, 6, or 7 infection.
- Positive test at screening for anti-HAV IgM Ab, HBsAg, anti-HBc IgM Ab, anti-HIV Ab
- Evidence of a medical condition associated with chronic liver disease other than HCV (e.g., hemochromatosis, autoimmune hepatitis, metabolic liver disease, alcoholic liver disease, toxin exposures)
- History or other evidence of decompensated liver disease
- Neutrophil count <1500 cells/mm3 or platelet count <90,000 cells/mm3 at screening
- Serum creatinine level >2 mg/dl (>124 µmol/L) or creatinine clearance ≤50 ml/minute at screening
- Severe psychiatric disease, especially depression, as judged by the treating physician.
- History of a severe seizure disorder or current anticonvulsant use
- History of immunologically mediated disease, severe chronic pulmonary disease associated with functional limitation, severe cardiac disease, major organ transplantation or other evidence of severe illness, malignancy, or any other conditions which would make the patient, in the opinion of the investigator, unsuitable for the study
- Thyroid dysfunction not adequately controlled (TSH and T4 levels out of normal range)
- Evidence of severe retinopathy (e.g. CMV retinitis, macula degeneration) or clinically relevant ophthalmological disorder due to diabetes mellitus or hypertension
- Evidence of drug abuse (including excessive alcohol consumption) in accordance with local therapeutic traditions.
- Inability or unwillingness to provide informed consent or abide by the requirements of the study
- Male partners of women who are pregnant
- emoglobin <12 g/dL in women or <13 g/dL in men at screening.
- Any patient with an increased baseline risk for anemia (e.g. thalassemia major, spherocytosis, history of GI bleeding, etc) or for whom anemia would be medically problematic coagulopathy.
- Patients with documented or presumed coronary artery disease or cerebrovascular disease should not be enrolled if, in the judgment of the investigator, an acute decrease in hemoglobin by up to 4 g/dL (as may be seen with ribavirin therapy) would not be well-tolerated
- Evidence of allergy to PEG-IFN or ribavirin.

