## early virological response

## pharmacokinetic response to ribavirin

# STUDY MEDICATIONS

## Dose and Schedule of Study Medications

Patients will receive PEGASYS® 180 g in 0.5 mL (prefilled syringes) administered sc once weekly. Specific guidelines for adjusting the dose of PEGASYS® are provided in Section 8.3. All PEGASYS® administrations will be via the sc route utilizing sterile technique. Test drug may be self-administered by the patients, except for the first dose, which should be administered in the clinic under the supervision of study personnel. Before providing the patient with test medication, the investigator or a qualified staff member will instruct the patient on the proper methods of storage of the medication, self-injection, and management and disposal of needles and syringes.

Patients will in combination with PEGASYS receive COPEGUS (ribavirin) which is administered p.o. daily: 13 mg/kg body weight. In Group A, patients will receive COPEGUS (ribavirin) 26 mg/kg body weight for the first 2 weeks (“Loading”) followed by COPEGUS (ribavirin) 13 mg/kg body weight for the remaining treatment duration. In Group B, patients will receive monotherapy with COPEGUS (ribavirin) 13 mg/kg body weight for 4 weeks prior to initiation of PEGASYS combination therapy. In both Group A and B, a ribavirin concentration will be obtained at local lab on day 28 after the initiation of PEGASYS, allowing for dose adjustments as deemed fit by the treating physician with the goal of achieving a ribavirin concentration (≥ 2.5 mg/L or 10.25 μmol/L). In Group C all patients will receive COPEGUS (ribavirin) 13 mg/kg body weight in combination with PEGASYS for the entire treatment duration without a ribavirin concentration without assessment on day 28 (“Standard-of-Care”)

All patients in this study will receive ribavirin treatment with food. By definition, ribavirin, with food entails taking their doses within 1 hour before or 2 hours after a meal. The meal should be considered “regular” as opposed to “fat-restricted”. Dose adjustment guidelines for ribavirin are provided in section 8.3.

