## Blinding and Randomization

This is an open label study with randomization occurring during the screening period, i.e. 4-12 weeks prior to the initiation of pegylated interferon therapy. During randomization patients will be stratified according to gender, age above or below 40 years, and GUCI < or ≥ 1.0 . Randomization will be computerized and will be performed once all inclusion criteria and none of the inclusion criteria have been fulfilled in the e-CRF.

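### The serum creatinine exclusion gives two different limits as one: 2 mg/dl is about 177 µmol/L, not 124

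*Protocol*

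**What the plan says.** Protocol section 4.3 (Exclusion Criteria) excludes patients with "Serum creatinine level >2 mg/dl (>124 µmol/L) or creatinine clearance ≤50 ml/minute at screening". The Selection Criteria row of the synopsis prints the same criterion, beginning "Serum creatinine level >2 mg/dl (>124", with the same figures. The layout, with the second figure in parentheses after the first, presents 124 µmol/L as the SI equivalent of 2 mg/dl.

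The only other statement on renal function at entry is in section 4.1 (Target Population), repeated in the synopsis: patients with "significant cardiac disease, renal disease, seizure disorders, or severe retinopathy will not be included". It carries no number.

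Two further places matter for the consequence:

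- Section 7.3 (Blinding and Randomization) makes randomization depend on the entry criteria that "have been fulfilled in the e-CRF".
- Section 7.1 sets the loading regimen: "In Group A, patients will receive COPEGUS (ribavirin) 26 mg/kg body weight for the first 2 weeks". Appendix 3 turns this into 2000 mg/day for a patient of 61-75 kg.

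**The concern.** The pair is too far apart to be rounding. A patient whose creatinine lies between the two limits is admitted under one figure and excluded under the other, so an entry criterion meant to protect patients has no single meaning in that range.

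What is at stake is who may enter, and with what renal function they may be given ribavirin. The sharpest case is Group A, which takes twice the standard dose for 14 days. The local ribavirin concentration that could prompt a dose change is drawn only on day 28, after loading has ended. Section 8.5.2.3 names anemia as the main toxicity and says hemoglobin generally falls within the first one to two weeks, which is the loading period.

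**Working it through.** **Inputs.** From section 4.3: 2 mg/dl, 124 µmol/L, and a clearance limit of 50 ml/min. From outside the protocol: the molar mass of creatinine, 113.12 g/mol, a physical constant.

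**Conversion.** µmol/L = mg/dl × 10,000 / 113.12 = mg/dl × 88.4.

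- Forward: 2 × 88.4 = 176.8 µmol/L (the protocol prints 124).
- Backward: 124 / 88.4 = 1.40 mg/dl (the protocol prints 2).
- Gap: 176.8 − 124 = 52.8 µmol/L; ratio 176.8 / 124 = 1.43.

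The printed equivalence cannot be reproduced in either direction.

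**Is it a general fault of the document or of the text extraction?** Other unit pairs in the protocol convert correctly:

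- Ribavirin target (section 7.1): 2.5 mg/L with an assumed molar mass of 244.2 g/mol is 10.24 µmol/L; the protocol prints 10.25.
- Bilirubin (Appendix 1): with an assumed factor of 17.1, 2 and 3 mg per 100 mL are 34.2 and 51.3 µmol/L; the protocol prints 34 and 51.

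The faulty pair appears identically in two separate places. The error is specific to this criterion and is not a stray extraction fault.

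**Who is affected?** A patient with creatinine above 124 and up to 177 µmol/L whose clearance is 50 ml/min or less is excluded under either figure. The discrepancy decides eligibility only when clearance is above 50. The protocol names no clearance formula, so I assume Cockcroft-Gault:

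clearance = (140 − age) × weight × k / (72 × creatinine in mg/dl), with k = 1 for men and 0.85 for women.

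Setting clearance above 50 and solving for age gives age < 140 − 3600 × creatinine / (weight × k). The affected patients are those below these ages:

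| Creatinine | Man 65 kg | Man 75 kg | Man 90 kg | Woman 65 kg | Woman 75 kg |
| --- | --- | --- | --- | --- | --- |
| 1.5 mg/dl | 56.9 | 68.0 | 80.0 | 42.3 | 55.3 |
| 1.8 mg/dl | 40.3 | 53.6 | 68.0 | 22.7 | 38.4 |

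**Worked cases.**

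- Man, 45 years, 75 kg, 1.8 mg/dl (159 µmol/L): 95 × 75 / (72 × 1.8) = 55.0 ml/min. Eligible under 2 mg/dl, excluded under 124 µmol/L.
- Man, 40 years, 80 kg, 1.6 mg/dl (141 µmol/L): 100 × 80 / (72 × 1.6) = 69.4 ml/min. The same conflict.
- Woman, 45 years, 65 kg, 1.5 mg/dl: 95 × 65 × 0.85 / (72 × 1.5) = 48.6 ml/min. Excluded by clearance whichever creatinine figure is used.

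The table shows who could be caught by the discrepancy. It does not show how many such patients there are, because the protocol gives no distribution of creatinine, age or weight.

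**The case against.** The mismatch itself cannot be defended, but its importance can be questioned on four grounds.

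- **A safe reading exists.** Any one exclusion criterion is enough to bar a patient, so a cautious investigator can exclude above 124 µmol/L. That is workable, but the protocol does not instruct it, and it would leave the 2 mg/dl figure with no function.
- **Other safeguards cover the band.** Every affected patient has already passed the clearance limit. Renal disease is excluded in general terms, and section 4.3 lets the investigator exclude anyone judged unsuitable. During treatment, creatinine is a listed safety assessment, hemoglobin rules govern dose reduction and stopping, and a DSMB reviews safety once the first 30 patients reach weeks 2 and 12. All of this stands and lowers the risk. None of it says which creatinine limit applies at entry.
- **Divergence between sites is not shown.** The protocol does not state laboratory units. If every site worked in µmol/L, all would apply 124. If the e-CRF holds a numeric limit, it would impose one rule; if it holds a tick-box, it would not. Inconsistent practice is therefore possible, not demonstrated.
- **No analysis is touched.** This is correct: no endpoint, analysis population, error rate or sample size depends on the figure.

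These points limit the consequence. They do not remove the conflict for patients between the two limits.

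**Conclusion.** The concern holds: the criterion is wrong as written. For a creatinine above 124 and up to 177 µmol/L with clearance above 50 ml/min, the protocol gives two contradictory answers on eligibility and no rule for choosing between them. The conversion rests only on the molar mass of creatinine. The description of who is affected rests also on the assumed Cockcroft-Gault formula. The number affected among the 105 patients is unknown and may be small.

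The effect is confined to eligibility and safety. Because eligibility is settled before randomization, the comparison between arms is not biased by it. It should still be corrected, since it is a wrong threshold in a working safety criterion and not a slip in background text.

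**What to change.** Choose one limit and print a consistent pair in both the synopsis and section 4.3: either **>2 mg/dl (>177 µmol/L)** or **>1.4 mg/dl (>124 µmol/L)**. The clinical choice belongs to the sponsor. Then confirm that the e-CRF eligibility check preceding randomization applies the same value.

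The cost is one line corrected in two places and one check of the e-CRF rule. Sample size, visit schedule and analysis do not change.

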## Concomitant Medication and Treatment

Systemic antiviral, anti-neoplastic and immunomodulatory treatments (including steroids and radiation) are not allowed during the study. Other investigational drugs against HCV are excluded.

Erythropoetin and/or filrgrastim are allowed as concomitant medication to manage side effects during treatment.

The total daily dose of acetaminophen (paracetamol) should not exceed 4 grams per day.

For patients receiving both theophylline and PEGASYS®,,Theofylline levels should be monitored and appropriate dose adjustment should be considered.

A complete listing of all concomitant drugs received must be recorded in the CRF.

**Paracetamol medication less than or equal to 4 gram/day should not be recorded in the CRF.**

**Ibuprofen medication less than or equal to 1.2 g/day should not be recorded in the CRF**

Alcohol consumption is to be strongly discouragedduring the study. This is because of possible adverse effects of alcohol on the response to therapy with IFNs in CHC. Patients will be queried on a regular basis concerning their alcohol consumption.

# SCHEDULE OF ASSESSMENTS AND PROCEDURES

## Schedule of Assessments

Baseline assessments should be obtained on the first day of drug administration prior to the initiation of antiviral therapy with PEGASYS and Copegus. This study will employ a serum- and plasma bank for the event that some tests need to be repeated and for herein described analysis.

## Screening Examination and Eligibility Screening Form

The following screening assessments (Table ) must be obtained within 56 days prior to the initiation of test drug administration.

Table 4 Screening Assessments

| Medical History Vital Signs And Physical Examination | Height, waist measurement, vital signs (systolic and diastolic blood pressure, heart rate, and body weight) and ophthalmological moscopic examination according to local standard |
| --- | --- |
| Clinical Chemistry | ALT, AST, gamma GT, total bilirubin, alkaline phosphatase, Calcium, albumin, creatinine, uric acid, cholesterol*, triglycerides*, glucose*, HbA1c*, Ferritin, Iron, TIBC, vitamin B-12, Folic Acid,  Ceruloplasmin†, alpha1-antitrypsin† |
| Hematology | Hemoglobin, hematocrit, erythrocyte volume (ery-MCV), reticulocytes, leukocytes, neutrophils, basophils, eosinophils, monocytes, lymphocytes, platelets, prothrombin time International Normalized Ratio (PK-INR) |
| Virology | HCV genotype, quantitative HCV-RNA (**COBAS TaqMan)** |
| Immunology | Anti-HAV IgM Ab, anti-HBc IgM Ab, HBsAg, anti-HCV Ab, anti-HIV Ab, anti-mitochondrial Abs, anti-nuclear Abs, anti-smooth muscle Abs |
| Thyroid Function Tests | TSH+, T4 (free) |
| Urinanalysis | Dipstick with subsequent microscopic evaluation if positive for hemoglobin |
| HCG Pregnancy Test | For women of childbearing potential, a negative urine (or serum) HCG test needs to be documented **within 24 hours prior** to the first dose |
| Liver Biopsy (optional) | Within 2 years prior to this study is encouraged, but optional in accordance with local treatment traditions |
| Liver ultrasound or CT or MRI | For patients with cirrhosis or transition to cirrhosis |
| Alpha-1-fetoprotein  (optional) | For patients with cirrhosis or transition to cirrhosis |

+For patients who exhibit elevated TSH the investigator should consider obtaining an anti-thyroid peroxidase antibody titre.

* Fasting values for cholesterol, triglycerides, glucose and HbA1c

The following examinations should be considered for certain patients at risk in order to establish compliance with the inclusion/exclusion criteria:

| Electrocardiogram | Only for men 40 years of age, women 50 years of age, and anyone else with a history of pre-existing cardiac disease |
| --- | --- |
| Immunology | Ceruloplasmin†, alpha1-antitrypsin† |

Notes:

†Ceruloplasmin and alpha1-antitrypsin do not need to be evaluated if these have ever been documented to be normal in the past

Patients at risk of ophthalmologic disorders (e.g diabetes mellitus and hypertension), with mild to moderate retinopathy should at screening have a thorough eye examination, including fundoscopic examination, should be performed to establish a baseline prior to treatment in this study.

Patients with history of psychiatric disease

Pegylated interferon should be used with caution in patients who report a history of depression. Physicians should monitor all patients for evidence of depression and should inform patients of the possible development of depression prior to initiation of pegylated interferon therapy. Patients should report any sign or symptom of depression immediately.

